**Translation of the approved study protocol (only methods section in agreement with editor)**

**Methods:**

*Design and recruiting:* The study is a randomized multicenter trial with 6 month follow-up with the participation of Regionalhospitals Silkeborg, Viborg, Horsens, Herning, and Aalborg University Hospital. A total of 140 patients with medically treated lung embolism (LE) will be included in the study, 70 in each group (Figure 1). The inclusion criteria are as follows: 1) objectively verified acute PE (ICD10 I260 and ICD10= I269); including recurrent LE; 2) treatment of LE with anticoagulant drugs; 3) 18–80 years of age; and 4) competency in the Danish language. Patients will be excluded in the case of: 1) PE as a secondary finding in relation to a scan performed due to another disease; 2) severe co-morbidity (e.g., severe heart disease, severe, active cancer, severe psychiatric disease, e.g. schizophrenia or depression). The nurses or physiotherapists at the cardiac wards of the participating hospitals will perform daily screening of patients hospitalized at the ward with the aim to recruit eligible patients according to the above criteria. On the day of discharge eligible patients are informed about the study, and the written study information is handed out (Appendix 1). Patients have a right to two days of deliberation time, and will be contacted by telephone hereafter to ask for participation in the project. By acceptance of participation written consent is retrieved (appendix 2) when the patients arrive for their baseline test in the AK-clinic (anti-coagulation clinic) app. 14 days after discharge. Following the baseline tests, patients are randomized to either the control group or the intervention group using opaque, sealed envelopes. Block randomization by hospital is used to ensure that approximately an equal number of patients at each hospital will be allocated to the control- and the intervention group, respectively.

[Figure 1. Flowchart as in manuscript]

**Outcomes and methods of measurement:** Data on patient's age, sex, BMI, medical treatment of LE, diagnosis (cause of LE) are retrieved from medical records at baseline.

- Primary outcome: Change in physical capacity, measured with the Incremental Shuttle Walk Test (appendix 3) from baseline to 6 months follow-up.
- Secondary outcomes: Change from baseline to 6 months follow-up on the following parameters:

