  - Disease-specific quality of life measured with the Pulmonary Embolism Quality of Life questionnaire
  - Generic quality of life measured with EuroQol-5 Dimensions
  - Sick leave (number of days in the past 4 weeks)
  - Use of painkillers and psychoactive drugs the past 4 weeks.

36  
37  
38  
39  
40  
41  
42  
43  
44  
45  
46  
47  
48  
49  
50  
51  
52  
53  
54  
55  
56  
57  
58  
59  
60  
61  
62  
63  
64  
65

The secondary outcome measures are collected in one questionnaire (appendix 4)  
The primary endpoint is 6 months after baseline test. In addition an intermediary measurement is performed 8 weeks after baseline (after termination of exercise program, see figure 1).

*The Incremental Shuttle Walk test (ISWT)* has been developed for assessing and measuring changes in a person's maximum walking capacity. The reliability and validity of the test has been shown in several studies and has been found acceptable. Studies show a reasonable association between maximal oxygen uptake and the ISWT, and that this association is better than the association between maximum oxygen uptake and the 6 minute walking test. The test has been validated within a number of study populations, including patients with heart and lung diseases [18].

The Pulmonary Embolism Quality-of-Life (PEmb-QoL) is a disease-specific quality of life questionnaire, containing six dimensions, covering frequency of complaints (8 items), activities of daily living (ADL) limitations (13 items), work-related problems (4 items), social limitations (1 item), intensity of complaints (2 items), and emotional complaints (10 items).

The EuroQol Five Dimensions (EQ-5D) is a generic quality of life questionnaire comprising both a descriptive part with 5 dimensions and the visual analogue scale EQ-VAS. The five dimensions mobility, self-care, usual activities, pain/discomfort, and anxiety/depression) [22, 23].

Sick leave and use of psychotropic drugs is gathered in questionnaires. Regarding sick leave the patient is asked to state the number of days' sick leave within the last four weeks according to the following categories: 0 work days; 1-4 days per week; 5-7 days per week. Regarding use of psychotropic drugs (e.g antidepressive medicine, anxiety reducing medication, sleeping pills) the patient is asked to state their average weekly use within the last four weeks according to the following categories: 0 days per week, 1-4 days per week, and 5-7 days per week.

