77      during hospitalization can vary between hospitals. The patients are scheduled for physical tests and  
78      completion of questionnaires at 8 weeks and 6 months.

79      *Group 2, homebased exercise:* In addition to usual care, patients are offered participation in an  
80      eight-week home-based exercise program with telephone follow-ups after 1, 2 and 4 weeks.  
81      Following the completion of the baseline measurements the physiotherapist has a dialogue with the  
82      patient regarding the importance of exercise and how the patient can schedule the exercise in their  
83      everyday life. In brief, the patients are recommended to exercise for a minimum of three times per  
84      week for 1 hour, with intervals (20 minutes in total) at a high intensity level, where only very short  
85      sentences of speech are possible). The remaining 40 minutes are at a moderate intensity, where you  
86      are only slightly out of breath, but having a conversation is possible. The patients can choose  
87      whatever type of exercise they prefer, and they are generally encouraged to choose an exercise  
88      modality they already perform, or a modality they have previously had positive experiences with.  
89      The patients record all their training sessions in a diary handed out at the first visit (appendix 5).  
90      The training diary can be handed out in paper or be sent on email. The training diary will be used  
91      for the motivational follow-up calls made by the physiotherapist at 1, 2 and 4 weeks. After the 8  
92      weeks program is finished, the patient brings the diary to the hospital at the subsequent follow-up  
93      test. Patients in the intervention group are scheduled for physical tests and completion of  
94      questionnaires at 8 weeks and 6 months like the control group.

95

96 **Analysis and evaluation:** For the primary outcome, ISWT, parametrical statistics are used to  
97 describe and analyse data, if data are normally distributed. For the secondary outcomes, PEmbQoL  
98 and EQ-5D, data are on an ordinal scale, and hence data are described and analyzed using non-  
99 parametric statistics. Sick leave (number of days) are described and analyzed using parametrical  
100 statistics if data are normally distributed. For the evaluation of psychoactive drugs the chi2 test is  
101 used. The power calculation is based on the ISWT. The smallest clinical relevant difference has  

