De sekundære effektmål er samlet i ét spørgeskema (Bilag 4).

Det primære endpoint er 6 måneder efter baseline måling. Herudover foretages også en intermediær måling 8 uger efter baseline (efter endt træningsforløb, se Figur 1).

*Incremental Shuttle Walk Test* (ISWT) er udviklet med henblik på at vurdere og måle ændringer i maksimal gangkapacitet [11]. Testens reliabilitet og validitet er belyst i flere studier og er generelt fundet acceptabel. Studier viser, at der er fornuftig sammenhæng mellem maximal iltoptagelse og ISWT, og denne sammenhæng er bedre end sammenhængen mellem maximal iltoptagelse og eksempelvis 6 minutters gangtest. Testen er valideret i en lang række sygdomspopulationer, herunder hos patienter med lunge- og hjerte/kar sygdomme [12].

*Pulmonary Emboli Quality-of-Life (PEmb-QoL)* er et sygdomsspecifikt livskvalitetsspørgeskema bestående af 9 overordnede dimensioner, der dækker emnerne *hyppighed af symptomer* (8 spørgsmål), *begrænsninger i dagligdags aktiviteter* (13 items), *arbejdsrelaterede spørgsmål* (4 items), *sociale begrænsninger* (1 item), *intensitet af symptomer* (2 items) og *emotionelle symptomer* (10 items)[13-15].

*EuroQol 5 Dimensions (EQ5D)* er et generisk livskvalitetsspørgeskema, bestående dels af en deskriptiv del med 5 dimensioner samt den visuelle analog skala EQ-VAS. De 5 dimensioner dækker over mobilitet, selvhjulpenhed, sædvanlige aktiviteter, smerter/ubehag og angst/depression [16, 17].

*Sygefravær og forbrug af psykofarmaka* indhentes ved brug af spørgeskema. For sygefravær bedes patienten angive deres samlede sygefravær indenfor de sidste 4 uger i følgende kategorier 0 dage; <5 arbejdsdage; <10 arbejdsdage; ≥10 arbejdsdage. For forbrug af psykofarmaka (fx antidepressiva, angstdæmpende medicin, sovemedicin) bedes patient angive deres ugentlige forbrug i de sidste 4 uger i kategorierne 0 dage, 1-4 dage per uge, 5-7 dage per uge.

Baselinemålingerne udføres af den fysioterapeut, der ser patienten i ambulatoriet, ca. 14 dage efter deres udskrivelse. De efterfølgende tests ved 8 uger og 6 måneder udføres af en projektfysioterapeut, der er blindet for, om patienten er i forsøgs- eller kontrolgruppen. Ved indkaldelse til opfølgende tests indskræpes det derfor overfor patienten, at de *ikke* må afsløre overfor den testende fysioterapeut, hvilken gruppe de har været i.

Tabel 1. Overblik over måletidspunkter:

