**Analyse og evaluering:** For det primære outcome, ISWT, anvendes parametrisk statistik til at beskrive og analysere data, såfremt data er normalt-fordelte. For de sekundære outcome, PEmb-QoL og EQ-5D, er der tale om ordinale data, og data beskrives og analyseres derfor med non-parametrisk statistik. Sygefravær (antal dage) beskrives og analyseres ved hjælp af parametrisk statistik, såfremt data er normalt-fordelt. Til evaluering af forbrug af psykofarmaka anvendes chi2 test. Power beregningen baseres på det ISWT. Den mindste klinisk relevante forskel er angivet til at være mellem 50 m. (KOL-rehabilitering) og 70 m. (hjerterehabilitering). Da en klinisk relevant forskel ikke er undersøgt for LE patienter valgtes en arbitrært sat klinisk relevant forskel på 60 m. Med en power på 80 % og signifikansniveauet sat til 5 % kræves en stikprøvestørrelse på 60 deltagere i hver gruppe. Med et forventet frafald på 10 % i hver gruppe sigtes der således mod at inkludere i alt 140 patienter.

**Etik:** Patienterne informeres mundtligt og skriftligt om undersøgelsens formål, og der indhentes skriftligt samtykke hos de deltagende patienter til at anvende deres data. Patienterne informeres om, at det er frivilligt at deltage, og at de til enhver tid har ret til at trække deres samtykke tilbage. Studiet er anmeldt til Region Midts paraplyanmeldelse til Datatilsynet den 26/08/2015 (godkendelse afventes), samt til Videnskabs Etisk Komité for Region Midtjylland (godkendelse afventes).

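### Sick leave is defined and analysed as a number of days but collected only in ordered categories, so the stated outcome and analysis cannot be produced

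*Protocol*

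**What the plan says.** Only the protocol is at hand: an English translation of the methods section, followed by the Danish text.

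- **Definition.** Under Outcomes and methods of measurement, the list headed "Secondary outcomes: Change from baseline to 6 months follow-up on the following parameters" includes "Sick leave (number of days in the past 4 weeks". The outcome is thus a change in a day count.
- **Collection.** The same section has the patient answer in three categories: "0 work days; 1-4 days per week; 5-7 days per week". The Danish section Effektmål og målemetoder gives four: "0 dage; <5 arbejdsdage; <10 arbejdsdage; ≥10 arbejdsdage".
- **Analysis.** Analysis and evaluation states: "Sick leave (number of days) are described and analyzed using parametrical" methods, conditional on normality. The Danish Analyse og evaluering agrees: "Sygefravær (antal dage) beskrives og analyseres ved hjælp af parametrisk statistik", with the same condition. Neither says what happens if the condition fails.
- **Comparison within the same paragraph.** The two quality-of-life instruments are called ordinal and given non-parametric methods. Psychotropic drug use is collected in none, 1–4 and 5–7 days a week, almost the same answers as sick leave, and is given a chi-squared test.

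**The concern.** The definition and the analysis need a number of days for each patient at each visit. The collection text says that only a category is obtained. A category does not contain the day count, and no later analysis can restore it.

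Sick leave is named in the study aim (end of the Danish Baggrund section), so it is an outcome that readers will expect to see reported. As the text stands, the analyst has two courses, and neither is the stated analysis: assign codes or midpoints and treat them as days, or choose another method after seeing the data.

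**Working it through.** The documents give no figure for sick leave, so there is nothing to reproduce. The check is what the categories can say about days.

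**1. Days over 4 weeks in each English category.** Inputs: the three answers and the 4-week recall period. Assumption: the weekly rate is constant, so days = 4 × days per week.

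| Answer | Lowest | Highest |
|---|---|---|
| none | 0 | 0 |
| 1–4 a week | 4 × 1 = 4 | 4 × 4 = 16 |
| 5–7 a week | 4 × 5 = 20 | 4 × 7 = 28 |

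**2. Change from baseline to 6 months.** Lowest possible change = lowest value at follow-up − highest value at baseline; highest possible change = highest at follow-up − lowest at baseline.

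- middle to middle: 4 − 16 = −12, to 16 − 4 = +12
- top to middle: 4 − 28 = −24, to 16 − 20 = −4
- middle to none: 0 − 16 = −16, to 0 − 4 = −4
- top to top: 20 − 28 = −8, to 28 − 20 = +8

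A patient recorded as unchanged in the middle category may have gained or lost up to 12 days.

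**3. Group mean.** Lower bound = sum of share × lowest value; upper bound = sum of share × highest value. The shares (none / middle / top) are assumed, since the documents give none.

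- 50/30/20%: 0.3 × 4 + 0.2 × 20 = 5.2, to 0.3 × 16 + 0.2 × 28 = 10.4 days
- 70/20/10%: 0.2 × 4 + 0.1 × 20 = 2.8, to 0.2 × 16 + 0.1 × 28 = 6.0 days
- 30/40/30%: 0.4 × 4 + 0.3 × 20 = 7.6, to 0.4 × 16 + 0.3 × 28 = 14.8 days

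**4. The normality condition.** Three-valued data are not normal by construction. To see whether a test would detect this, midpoints of 0, 10 and 24 days were simulated for 60 patients (the protocol's per-group number before drop-out), 1000 runs per pattern. Shapiro–Wilk rejected at 5% in 100% of runs for shares of 50/30/20, 70/20/10, 33/34/33 and 25/50/25. This covers scores at one visit. Change scores were not simulated; from these midpoints they can take at most seven values (0, ±10, ±14, ±24). Even if a test on them did not reject, the input would still not be a number of days.

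**5. The Danish categories.** Read as 0, 1–4, 5–9 and 10 or more working days, they are narrower but the top one is open-ended, so a mean in days is again not available. The English middle category (4–16 days) overlaps all three non-zero Danish bands, so the two sets cannot be converted into each other. The unit differs as well: the Danish set counts working days over 4 weeks, while the English set mixes work days with days per week up to 7.

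**The case against.** **The parametric rule is conditional.** By the protocol's own wording, a parametric test would not be run on data that fail normality. A reader might infer that the plan commits to a t-test on category codes; it does not. That stands. But the condition cannot be met and no alternative follows it, so no usable analysis is fixed.

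**A fallback method is commonly left to the analysis plan.** True, and a missing fallback alone would be no finding. Here the protocol itself fixes the outcome, the answers and the method, and they conflict. An analysis plan could choose another test, but it could not supply days that the form did not record.

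**The Danish text looks like an earlier version.** It says ethics approval is awaited, lists a different set of hospitals and has a different upper age limit; the English is headed as a translation of the approved protocol. A reader might infer that two questionnaires ran side by side. The documents do not show this. The Danish text matters because it contains the same conflict, so the conflict is not a slip of translation.

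**Some flaws in the categories depend on strict reading.** A patient absent 1–3 days in total has no English category only if the rate must be constant over 4 weeks; someone absent two days in one week could reasonably tick the middle answer. The Danish bands below 5 and below 10 overlap literally but are naturally read as successive. Both are loose wording to tidy, not demonstrated failures.

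**Retired patients.** With inclusion to age 80, a reader might infer that people out of work are recorded as zero and dilute the effect. The questionnaire (appendix 4) is not shown and may have an employment item, and the documents give no share out of work. This can only be a conditional point.

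**The baseline window.** The 4 weeks before baseline hold about 14 days since discharge and 3–5 hospital days, leaving 28 − 14 − 5 = 9 to 28 − 14 − 3 = 11 days before admission. A reader might infer a biased change score. Baseline precedes randomisation and both arms share the window, so it does not bias the comparison between arms.

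**Conclusion.** Wrong as written. The protocol cannot deliver a change in sick-leave days, or a parametric analysis of it, from the answers it collects. On the constant-rate reading, an unchanged middle category hides a change of up to 12 days either way, and a group mean is known only within limits such as 5.2 to 10.4 days under assumed shares of 50/30/20%.

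The contradiction itself needs no assumption; it follows from the definition, collection and analysis texts. Only the sizes depend on the constant rate and the assumed shares.

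The reach is limited to one secondary outcome. Power is based on the walking test, and the primary analysis and the sample size are untouched. It would go too far to infer that the trial's main conclusion is at risk.

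**What to change.** Choose one of two routes and make definition, collection and analysis agree.

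1. **Keep days.** Replace the categories with one numeric field for the number of sick-leave days in the past 4 weeks, stating whether working or calendar days are meant, and name the method to be used if the normality condition fails.
2. **Keep categories.** Redefine the outcome as the ordered category at 6 months, delete the parametric rule for sick leave, and compare arms with an ordinal or rank-based method that accounts for the baseline category, for example a proportional-odds model with baseline category as covariate. Use one category set with a single unit and non-overlapping bounds.

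If forms have already been completed in categories, only the second route is open. If both category sets were ever used, the only cut point they share is none versus some.

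In either case, check appendix 4. If it has no employment item, add one, so that zero does not mix people at work with people outside the workforce.

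The cost is a questionnaire line and a few changed sentences in the protocol. Under the second route the result is no longer expressed in mean days.

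### Psychotropic drug use is a change-from-baseline outcome on three ordered categories, but the protocol fixes a chi2 test that ignores the order and has no stated baseline term

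*Protocol*

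**What the plan says.** Under Outcomes and methods of measurement, the protocol introduces the list as "Secondary outcomes: Change from baseline to 6 months follow-up on the following parameters", and one entry is "Use of painkillers and psychoactive drugs the past 4 weeks". The measurement text asks patients for their average weekly use of psychotropic drugs (antidepressants, anxiety medication and sleeping pills are the examples) "according to the following categories: 0 days per week, 1-4 days per week, and 5-7 days per week". Table 1 schedules medication at baseline, 8 weeks and 6 months, so each patient should have a baseline answer.

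Analysis and evaluation then says "For the evaluation of psychoactive drugs the chi2 test is" used. The Danish section Analyse og evaluering says the same: "Til evaluering af forbrug af psykofarmaka anvendes chi2 test". Neither version states which table is tested, at which time point, or how the baseline answer is used.

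Earlier in the same paragraph, PEmb-QoL and EQ-5D are handled by a reasoned rule: their "data are on an ordinal scale, and hence data are described and analyzed using non"-parametric statistics.

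**The concern.** The protocol does not leave the method open here; it chooses a test, and the choice does not fit the outcome it has defined. Two kinds of information are set aside.

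- **Order.** Moving from 5-7 days to 1-4 days is a smaller step than moving from 5-7 days to none. A Pearson chi2 test spreads its two degrees of freedom over any difference between the arms, including patterns with no direction.
- **Baseline.** The outcome is a change, and earlier use is likely to predict later use strongly. The named test has no stated place for it.

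The paragraph is also inconsistent in its reasoning. An ordered scale is the reason for the method chosen for two questionnaires, while a scale that is just as ordered gets a method that takes no account of order.

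What is at stake is the chance of detecting a real shift in psychotropic use, which the closing sentence of the Danish background names among the aims of the study.

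**Working it through.** **Inputs from the protocol.** 140 patients, 70 per group; 60 per group needed for the walk test; 10% drop-out, so 70 × 0.9 = 63 per group expected at follow-up; significance level 5%; three ordered categories. The protocol gives no power figure for drug use, so there is none to reproduce. Its sample size rests on the walk test and is used here only as the number analysed.

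**Inputs that are assumed.** Usage rates (the documents give none), the size and direction of the effect, and the baseline-to-6-month correlation. The effect is taken as monotone, with a common odds ratio of 0.4 for higher use.

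**Step 1: what the chi2 statistic uses.** With observed count O and expected count E, X² = Σ(O − E)²/E over the cells of the arm-by-category table, with (2 − 1)(3 − 1) = 2 degrees of freedom. The sum does not depend on the order of the categories, and no term refers to the baseline answer.

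**Step 2: is the test valid with few users?** The expected count per arm in a category is n × p. It reaches 5 when p = 5/60 = 8.3% at 60 per arm, or 5/63 = 7.9% at 63. Simulated rejection rates under no effect, at a nominal 5%:

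| Per arm | Use (0 / 1-4 / 5-7 days) | Rejection rate of chi2 |
|---|---|---|
| 60 | 60/20/20% | 5.4% |
| 60 | 80/10/10% | 4.8% |
| 60 | 90/5/5% | 3.8% |
| 63 | 96/2/2% | 1.8% |
| 63 | 98/1/1% | 0.4% |

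At 80/10/10% about 41% of the null tables contain an expected count below 5, yet the error rate is correct. Where the approximation fails, the test rejects too rarely.

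**Step 3: power lost.** Simulation with 60 per arm, odds ratio 0.4, correlation 0.7:

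| Use | chi2 at 6 months | Rank test at 6 months | Baseline-adjusted rank analysis |
|---|---|---|---|
| 60/20/20% | 52% | 64% | 78% |
| 80/10/10% | 31% | 41% | 47% |

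- Loss against the rank test: 64 − 52 = 12 points and 41 − 31 = 10 points.
- Loss against the adjusted analysis: 78 − 52 = 26 points and 47 − 31 = 16 points.

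A smaller simulation (250 trials per scenario, Monte Carlo error about 3 points) put a proportional-odds model with baseline at 79% and 49% in these two settings, close to the adjusted rank analysis.

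**Step 4: does another table rescue the test?** The text would also allow a chi2 test of arm by decreased, unchanged or increased use. Simulated with 63 per arm and an assumed latent shift of 0.5 SD:

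| Users in total | Correlation | chi2 on change categories | Baseline-adjusted rank analysis |
|---|---|---|---|
| 20% | 0.5 | 28% | 45% |
| 20% | 0.8 | 38% | 59% |
| 30% | 0.5 | 35% | 56% |
| 30% | 0.8 | 50% | 71% |

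That reading brings baseline in, but it still ignores order and still loses about 17 to 21 points.

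**The case against.** The strongest reply is that the protocol names only a test. The table, the time point, the use of baseline, the effect measure and any small-count rule are details that an analysis plan commonly supplies, and none is at hand. That stands as far as it goes: it cannot be said that the baseline answer will be discarded, only that no baseline term is stated. It does not rescue the choice of test, because a chi2 test ignores order on either table.

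A second reply is that chi2 is itself often called non-parametric, so the paragraph does not literally contradict itself. That is fair. The inconsistency lies in the reason given: ordinality decides the method for two outcomes and is passed over for a third.

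A third is that the power comparison suits the recommended method, since a monotone shift is assumed, and that the trial was never powered for this outcome. Both parts are true. Chi2 could do better against an effect without direction, and with 20% users even the adjusted analysis stays below 50% power.

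Three stronger readings are tempting and are not supported:

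- *That the test breaks down or gives unreliable p-values.* Its error rate was about right at 20% users or more, and too low rather than too high below that.
- *That users will certainly be few.* Severe psychiatric disease is excluded, but sleeping pills and anxiety medication count towards the outcome, and no usage rate is given.
- *That painkiller use is not measured.* It shares the outcome entry and has no scale or test in the text, but the questionnaire is an appendix that is not shown. This is mostly missing detail and does not belong to this point.

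**Conclusion.** The point holds as a mismatch and a loss of power. An ordered outcome defined as change is given a test that uses no order and has no stated baseline term. Randomization still makes the chi2 test a valid comparison, so a significant result would not be suspect for this reason; the risk is that a real shift is missed.

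The loss is about 10-12 percentage points against a rank test and about 16-26 against a baseline-adjusted ordinal analysis. These figures rest on assumed usage of 20-40%, a monotone effect with odds ratio 0.4 and, for the second range, a correlation of 0.7. A weaker correlation would shrink the gain from adjustment; the gain from using order does not need it. Severity is low to moderate, because the outcome is secondary and the primary analysis is untouched.

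**What to change.** Replace the chi2 sentence, in both language versions, with text to this effect: *Psychotropic drug use at 6 months (three ordered categories) will be compared between groups with a proportional-odds model that includes the baseline category, and reported as an odds ratio with 95% confidence interval.* Conditioning on the baseline category is how the defined change enters the analysis.

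Add a fallback with a threshold fixed before the data are seen: if either user category at 6 months holds fewer than a stated number of patients, pooled over arms, compare any use with none by exact or Firth logistic regression. Pooling over arms keeps the choice independent of the group difference. Without a written number, the choice of analysis would depend on the data.

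Leave hospital out of this model. With five hospitals it would have 1 + 2 + 4 = 7 slopes. In simulation at 90/5/5% use, at least one coefficient diverged in 44% of fits under no effect and in 67% under an odds ratio of 2.5.

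The cost is two or three sentences and no new data, since Table 1 already schedules the baseline and 6-month answers. The small downside is the proportional-odds assumption; the raw counts by arm and category should be tabulated beside the estimate so that readers can judge it.

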The baseline measurements are performed by the physiotherapist who sees the patient at he baseline visit 14 days after their discharge. The following tests at 8 weeks and 6 months are performed by a project physiotherapist, who is blinded as to the patient's group allocation. When the patient is summoned for the follow-up tests it is underlined that the patients must not reveal their group allocation.

66      Tabel 1. Overview of measurement timepoints

| Timepoint      | Baseline
14 days after discharge | 1st follow-up
8 weeks after baseline | 2nd follow-up
6 months after baseline |
|----------------|-------------------------------------|-----------------------------------------|------------------------------------------|
| Outcome |                                     |                                         |                                          |
| Incr SWT       | X                                   | X                                       | X                                        |
| PEmb-QoL       | X                                   | X                                       | X                                        |
| EQ-5D          | X                                   | X                                       | X                                        |
| Sick leave     | X                                   | X                                       | X                                        |
| Medication     | X                                   | X                                       | X                                        |

67      *Incr SWT = Incremental Shuttle Walk Test; PEmb-QoL = Pulmonary Embolism Quality of Life*  
68      *Questionnaire; EQ-5D = EuroQol 5 Dimensions*

69

70      **Interventions**

71      *Group 1, usual care:* A usual course of treatment typically entails 3-5 days of hospitalization where  
72      anticoagulant treatment is initiated. The patient and his or her relatives receive general information  
73      about the disease and the course of treatment, the medication, and future prevention of embolism.  
74      Approximately 2 weeks after discharge the patient is seen at the hospital for control of their  
75      medication and the following outpatient visits are planned individually depending on the patient's  
76      needs. Any other treatment that may be offered at the hospitals, e.g. contact with physiotherapists  

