102 been reported to be between 50 m. (COPD rehabilitation) and 70 m. (cardiac rehabilitation). As a  
103 clinically relevant difference has not been investigated for LE patients and arbitrarily clinically  
104 relevant difference of 60 meters was decided upon. With a power of 80% and a significance level of  
105 5% a sample size of 60 patients is needed for each group. With an expected drop-out rate of 10% in  
106 each group we aim to include 140 patients in total.  
107

Effekten af et 8-ugers træningsforløb  
på fysisk kapacitet og livskvalitet  
hos patienter med lunge-emboli.  
En klinisk randomiseret undersøgelse

Projektgruppe:

[name], fysioterapeut

[name], sygeplejerske

[name], overlæge, dr. med.

[name], ledende terapeut

[name], forskningsansvarlig terapeut, ph.d.

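### As the primary outcome is defined, the 8-week walk test has no role in any stated analysis, and a patient tested at 8 weeks but not at 6 months has no primary value

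*Protocol*

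**What the plan says.** Under Outcomes and methods of measurement, the protocol defines the primary outcome as "Change in physical capacity, measured with the Incremental Shuttle Walk Test (appendix 3) from baseline to 6 months follow-up". The secondary outcomes are also changes from baseline to 6 months.

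The same section adds a third time point: "In addition an intermediary measurement is performed 8 weeks after baseline", at the end of the exercise programme. Table 1 schedules the ISWT at baseline, 8 weeks and 6 months for everyone. Both follow-up tests are by a blinded assessor: "The following tests at 8 weeks and 6 months are performed by a project physiotherapist".

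Under Analysis and evaluation, the method is "For the primary outcome, ISWT, parametrical statistics are used to" describe and analyse the data, provided they are normally distributed. No test or model is named, and the 8-week value is not mentioned.

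Drop-out appears only in the sample-size sentences of that section. For 60 m, 80% power and a 5% level they give "5% a sample size of 60 patients is needed for each group. With an expected drop-out rate of 10% in" each group, the aim is 140 patients. The Danish text agrees: "Med et forventet frafald på 10 % i hver gruppe sigtes der således mod at inkludere i alt 140 patienter".

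**The concern.** A change from baseline to 6 months can be calculated only for a patient who has the 6-month test. Someone who attends at 8 weeks and then stops coming has a blinded post-programme ISWT on file but no value on the primary outcome. The sample size likewise counts every drop-out as a full loss.

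Two things are at stake. The first is precision, because measured information goes unused. The second is bias. A completers-only comparison is safe if drop-out is unrelated to how patients are doing, or if it selects alike in both groups. There is some reason to doubt the latter: only the exercise group is asked for at least three one-hour sessions a week and receives motivational calls, and both end well before the 6-month test. If the patients who gained least by 8 weeks were the ones missing at 6 months, and this happened more in the exercise group, the effect would be overstated.

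**Working it through.** **Inputs from the protocol.** Difference 60 m; power 80%; level 5% (two-sided assumed, as sidedness is not stated); 60 evaluable and 70 randomised per group; 10% drop-out in each group, not tied to a visit.

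**Assumptions, not in the protocol.** SD of ISWT change, back-calculated below; correlation ρ between the 8-week and 6-month changes of 0.6 to 0.8; odds of dropping out that double for each SD lower 8-week change.

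**1. The plan's own figure.** With n = 2(1.960 + 0.842)²·SD²/60², n = 60 requires SD = 60 / (2.802 × √(2/60)) = 117.3 m. SDs of 116, 117 and 118 m give n = 59, 60 and 61. Because the SD is not given, the 60 cannot be confirmed independently.

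For drop-out, 60/0.90 rounds up to 67 per group. The planned 70 is above that and leaves 70 × 0.90 = 63 evaluable. It tolerates 1 − 60/70 = 14.3% loss before falling below 60.

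**2. The plan's assumption: 10% lost in each group, same mechanism.** In a large simulation (1,000,000 patients per arm, true effect 60 m), the completers-only difference stays at about 60 m. There is no bias, because both arms are shifted equally. What remains is precision. If all drop-outs have an 8-week value, the effective number per group is 70 / [(1 − ρ²)/0.9 + ρ²]:

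| Analysis | Effective n per group | Power |
|---|---|---|
| Completers only | 63 | 81.9% |
| With 8-week value, ρ = 0.6 | 65.4 | 83.2% |
| With 8-week value, ρ = 0.7 | 66.2 | 83.7% |
| With 8-week value, ρ = 0.8 | 67.3 | 84.3% |

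**3. Drop-out that differs by arm and follows the 8-week response.** Same simulation, ranges over ρ = 0.6 to 0.8:

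| Exercise / control drop-out | Completers only | 8-week value used, all drop-outs have it |
|---|---|---|
| 15% / 5% | about 64 to 66 m | about 60 m |
| 20% / 0% | about 69 to 72 m | about 60 m |

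At 15% against 5% the bias is 4 to 6 m, or 7 to 10% of 60 m. The standard error of the difference with 63 per group is 117.3 × √(2/63) = 20.9 m.

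**4. How much the 8-week value can repair.** At 15% against 5%, if half the drop-outs left before the 8-week test, the adjusted estimate is about 62 to 63 m. If all did, nothing is corrected (about 65 to 66 m).

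**5. Direction.** If the odds of leaving instead double for each SD higher 8-week change, the 15% against 5% completers-only estimate is about 54 to 55 m, and the bias is towards no effect.

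**6. Equal rates, unequal mechanism.** Equal percentages alone do not guarantee zero bias. With 10% lost in the exercise arm selectively (log-odds rising by 1 per SD lower 8-week change), an unselected loss in control and ρ from 0.5 to 0.9, the overstatement is about 5 to 10 m.

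**The case against.** The strongest reply is that the protocol does not do what a reader might infer, namely treat patients without a 6-month test as lost in the analysis. That is correct. The 10% is a recruitment allowance. Inflating the sample size for drop-out is routine and defines no analysis set. A mixed model is itself a parametric method and would fit the analysis section as worded. Rules for missing data are commonly left to a statistical analysis plan, which is not at hand, so their absence is no finding.

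A reader might also infer that selective loss after the programme is expected to bias this trial. The document does not support that either. It expects 10% in each group, not a 15/5 or 20/0 split, and does not say when patients leave. A demanding programme may well lose patients before 8 weeks, and for them no 8-week value exists. Either direction of selection is possible. Even at 15% against 5%, the bias is small beside a standard error of about 21 m.

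All of this stands, and it limits the point to an improvement. What it does not remove is that the protocol sets the outcome and the role of each visit, collects a blinded ISWT at 8 weeks in everyone, and puts that value to no stated use.

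**Conclusion.** The point holds as a recommendation, not as an error that undermines the trial. Followed as written, a two-point change comparison would give no value to a patient seen at 8 weeks but not at 6 months.

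On the plan's own drop-out assumption, with the same mechanism in both arms, the cost is only 2 to 4 effective patients per group and one to two points of power. Bias of several metres, in either direction, arises only if drop-out differs between the arms in rate or mechanism and follows the 8-week response. These sizes rest on an SD of 117 m, a correlation of 0.6 to 0.8 and the assumed drop-out model, none of which the protocol states.

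**What to change.** State in Analysis and evaluation that the primary outcome is analysed with a linear mixed model for repeated measures of ISWT at 8 weeks and 6 months. It should include all randomised patients with any follow-up ISWT, with baseline ISWT as covariate and a group-by-visit term. The group difference at 6 months stays the primary contrast.

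Add a sensitivity analysis for drop-out that depends on unobserved values. The model assumes that drop-out depends only on observed ISWT values, and it cannot recover patients lost before 8 weeks.

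Reporting the 8-week contrast from the same model as a named secondary outcome is optional. It would help to tell an effect that faded after the programme from no effect at all.

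The cost is a sentence or two of text and one extra analysis. No new visits, data or patients are needed.
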